### Outcome measures

#### Main outcome measure

Self reported ‘continuous abstinence’ defined by Hughes et al. 2003 [43] as *the abstinence between quit day and a follow*-*up time* (at six and twelve months) after intervention confirmed by a breath CO cooximetry concentration of 6 parts per million (ppm) or less in standard conditions.

*Other outcome measures*:

– Point prevalence abstinence according to Hughes et al. 2003 [43] defined as *prevalence of abstinence during a time window immediately preceeding follow*-*up* at three, six and twelve months after intervention confirmed by breath carbon monoxide cooximetry in standard conditions.

Self reported tobacco consumption at three, six and twelve months after intervention: daily consumption in cigarettes/day.

– Self-reported reduction of daily tobacco consumption in cigarettes/day when the subject does not stop smoking at three, six and twelve months after intervention.

– Change of stage in the Prochaska and DiClemente's Stages of Change Model at three, six and twelve months after intervention.

– Prescription of tranquilizers, antidepressants, NRT (nicotine replacement therapy), at the beginning and end of the intervention and six and twelve months post intervention.

– Registered use of sanitary services in primary and specialized care, both in public and private settings.

– Time used by professionals in the two face to face interviews (initial and three months visits).

– Time used by sanitary professionals in case they have to answer E-mail contacts.

– Time used by patients in case they have to ask questions during the E-mail intervention.

– Costs for the patients to access Primary Care service at three, six and twelve months after intervention.

*Independents*:

– Type of intervention: Intensive counseling by E-mail vs brief advice.

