### Data collection

At baseline visit, face to face interview with the sanitary professional will be carried out and the following information will be registered:

– Socio-demographic characteristics: age, gender, civil status, educational level, social class according to the classification of the UK Registrar General's social classification (RGSC).

– E-mail frequently used and data for the telephone tracking.

Characteristics of individual's tobacco consumption: daily consumption in cigarettes/day, years of smoking, age at the start, time before first cigarette of the day, nicotine, dependence measured by the Fagerström test [44], number of previous attempts to quit smoking, maximum time of abstinence, pharmacological treatment used on previous attempts to quit smoking: type, timetable, side effects, family and friends environmental tobacco consumption, partner interaction questionnaire (PIQ Test) to measure of spouse/partner support related to cessation [45].

– Change of stage in the Prochaska and DiClemente's Stages of Change Model.

– Alcohol consumption.

– Morbidity (related or not to tobacco consumption): chronic obstructive pulmonary disease, cerebrovascular event, ischemic cardiopathy, arterial hypertension, hypercholesterolemia, cancer and peripherical arteriopathy, diabetes mellitus, obesity.

– Weight.

– Breath carbon monoxide (CO) in ppm measured by cooximetry which will be carried out by trained health professionals using following a pre-established protocol.

At three months after intervention a second face to face interview will be undertaken with the sanitary professional and the following information will be recorded: time spent in the visit and if the subject currently smokes. If so, daily consumption in cigarettes/day and stage of change according to Prochaska and DiClemente's Stages of Change Model will be recorded. If not, date of smoking cessation, time (in days) of abstinence will be asked, and level of breath CO by cooximetry in standard conditions. Self-reported weight will be documented in both cases. Date of visit and the professional who undertakes it will be additionally recorded.

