### Statistical methods

Data will be analyzed in concordance with the Consort Cluster guide [46], and all analyses will be done on an intention to treat basis. Baseline descriptive statistics among CG and IG in relation to the variables studied will be computed as customary; in contingency tables Pearson’s Chi-square test for independence or homogeneity will be applied to assess the relationship between two categorical variables, T-Student test or ANOVA will be used in the comparison of means if the variables follow a normal distribution and U of Mann Whitney test if they do not. For the other dimensions of the analysis, a covariance analysis (ANCOVA) for repeated measures will be carried out.

A multilevel logistic regression and a Poisson regression will be done to evaluate the association between each of the dependent variables and the independent variables that have resulted statistically significant in the bivariate analysis. All analysis will be adjusted for potential confounding factors and for variables with clinical relevance. The level of statistical significance will be set at 0.05, and all tests will be two-tailed. Statistical analyses will be conducted using SPSS, version 17.0 (SPSS Inc, Chicago, IL).

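### The reduction outcome is compared between arms only among patients who did not quit, a group that treatment itself helps to form, so that secondary comparison is not a randomised one

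*Protocol article*

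**What the plan says.** The list of other outcome measures in the protocol article (*Outcome measures*) contains two neighbouring items on consumption:

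- unrestricted: "Self reported tobacco consumption at three, six and twelve months after intervention: daily consumption in cigarettes/day";
- restricted: "Self-reported reduction of daily tobacco consumption in cigarettes/day when the subject does not stop smoking", at the same three time points.

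The same section lists one independent variable: "Type of intervention: Intensive counseling by E-mail vs brief advice". *Statistical methods* plans regressions "to evaluate the association between each of the dependent variables and the independent variables", limited to independent variables that were significant in bivariate analysis, and adds that "all analyses will be done on an intention to treat basis". No item is singled out as descriptive.

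On the data, *Data collection* records consumption for everyone at baseline: "Characteristics of individual's tobacco consumption: daily consumption in cigarettes/day, years of smoking". At the three-month visit the patient is first asked whether he or she currently smokes, and then: "If so, daily consumption in cigarettes/day and stage of change according to Prochaska and DiClemente's Stages of Change Model will be recorded". For those not smoking, a quit date, days of abstinence and CO are recorded instead. No rule gives abstainers a value of 0 cigarettes/day.

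**The concern.** The restricted outcome exists only for patients who are still smoking at the visit. Whether a patient belongs to that group is settled after randomisation, by the behaviour that the intervention is designed to change. If the intervention works, it removes from its own arm some patients who would have stayed in the comparison under brief advice. The remaining smokers in the two arms can then differ in readiness to quit, dependence or baseline consumption, for reasons unrelated to any effect on cutting down.

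A difference in mean reduction between these groups mixes an effect on smokers with a change in who is counted. The more the intervention helps people quit, the more room there is for that distortion. At stake is the reading of one secondary result, which could be reported as showing that e-mail support does or does not help continuing smokers cut down.

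**Working it through.** **Inputs from the protocol article.** *Sample size*: 5% continued abstinence in control, a difference of 5 points (so 10% under intervention), two-sided alpha 0.05, power 0.80, dropout 20%, 530 per arm. *Inclusion of participants and randomization*: 1:1 allocation.

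**Reproducing the plan's figure.** With the arcsine formula, n = (1.960 + 0.842)² / (2 × (asin√0.10 − asin√0.05)²) = 424 per arm, and 424 / 0.80 = 530 per arm, 1060 in total. This matches exactly. The pooled normal formula gives 435, or 544 after dropout, within 3%. The design quit rates are therefore read correctly as 5% and 10%.

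**Who is left in the restricted comparison.**

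- Of 530 randomised: control 530 × 0.95 = 503.5; intervention 530 × 0.90 = 477.
- Of the 424 per arm left after 20% dropout: control 402.8; intervention 381.6.

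The compared sets thus differ by design whenever the trial succeeds.

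**Size of the selection effect.** Assume that each patient has a standard normal quit propensity, with correlation ρ to the reduction he or she would show if still smoking. The top 5% (control) or 10% (intervention) quit, and the intervention has no effect on reduction itself. Among the rest, the mean propensity is −φ(z)/(1 − q), where q is the quit rate and z the normal quantile at 1 − q:

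- q = 0.05: −0.1031 / 0.95 = −0.1086
- q = 0.10: −0.1755 / 0.90 = −0.1950
- q = 0.20: −0.2800 / 0.80 = −0.3500

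The bias, intervention minus control, in SDs of reduction is ρ × (−0.1950 + 0.1086) = −0.0864ρ at 5% vs 10%, and ρ × (−0.3500 + 0.1086) = −0.2414ρ at 5% vs 20%. The document gives neither ρ nor the SD, so both are assumptions. The 20% is also an assumption: *Background* says more intense interventions can exceed 20%, but that is not the design rate.

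| Assumed ρ | 5% vs 10%, in SD | cigarettes/day at SD 6 | 5% vs 20%, in SD | cigarettes/day at SD 6 |
|---|---|---|---|---|
| −0.3 | +0.026 | +0.16 | +0.072 | +0.43 |
| 0 | 0 | 0 | 0 | 0 |
| 0.3 | −0.026 | −0.16 | −0.072 | −0.43 |
| 0.5 | −0.043 | −0.26 | −0.121 | −0.72 |
| 0.8 | −0.069 | −0.41 | −0.193 | −1.16 |

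A minus sign means that the intervention looks worse. Simulation agreed with the formula for ρ from 0 to 0.8; the negative row follows by symmetry.

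**How a sign can reverse.** This is one invented scenario. Baseline is 17 cigarettes/day. In both arms 5% quit anyway and 90% cut by 1.7. The other 5% halve their smoking (a cut of 8.5) under control but quit under intervention.

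- Non-quitters: control (5 × 8.5 + 90 × 1.7) / 95 = 2.06; intervention 1.70. The intervention looks worse by 0.36.
- All randomised, quitters at 0: control 0.05 × 17 + 0.05 × 8.5 + 0.90 × 1.7 = 2.805; intervention 0.10 × 17 + 0.90 × 1.7 = 3.23. The intervention is better by 0.425.

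This shows what is possible, not what is expected: it assumes that every extra quitter would otherwise have been a strong reducer.

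**The case against.** The strongest reply is that the article already lists an all-patient consumption outcome directly before the restricted one. Baseline cigarettes/day are collected, all participants are asked about consumption at 6 and 12 months, and covariate adjustment is planned. In a linear model adjusted for baseline, follow-up consumption and change from baseline give the same treatment effect apart from sign. Most of the remedy is therefore already there. This stands, and a reader who inferred that the trial has no consumption comparison free of this restriction would be wrong. But the restricted item remains a separate outcome. At three months, moreover, the count is recorded only for current smokers, so without a zero for abstainers the unrestricted outcome could shrink to the same group.

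A second reply is that no between-arm test is specified for this item. That is so; the test is inferred from the general statement about each dependent variable and from arm being the listed independent variable. The inference is reasonable, and nothing marks the item as descriptive.

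A reader might also infer that the plan contradicts its own intention-to-treat statement. The document does not support that: patients in a subset can still be analysed by assigned arm, so both statements can be true. The difficulty is that doing so does not restore the randomised comparison.

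Lastly, the bias need not run against the intervention. If lighter smokers are the ones who quit, those remaining have more cigarettes to cut, and if reductions are proportional to baseline the intervention arm would look better.

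**Conclusion.** The point holds for this one secondary outcome. As written, the plan compares arms within a group defined by a post-randomisation event that the intervention is meant to change.

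At the design quit rates the bias is probably small: about 0.03 to 0.07 SD for assumed correlations of 0.3 to 0.8, or 0.16 to 0.41 cigarettes/day at an assumed SD of 6. It vanishes at zero correlation, reverses if the correlation is negative, and grows with the quit-rate difference. These figures also take the design's continuous-abstinence rates as the share not smoking at a visit; a wider gap in actual smoking status would enlarge them.

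Two stronger conclusions are not supported. The document does not settle that the comparison will disfavour the intervention. Nor is the main result touched: CO-confirmed continuous abstinence and the sample size of 530 per arm do not depend on this outcome.

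**What to change.** Make the unrestricted cigarettes/day outcome the between-arm comparison of consumption, in all randomised patients at 3, 6 and 12 months. State that abstainers are scored 0 cigarettes/day at each visit, and adjust for baseline cigarettes/day. Report reduction among continuing smokers by arm as descriptive only, without a between-arm test, and say why.

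This takes a change of outcome wording and one derivation rule, settled before the outcome data are analysed by arm. Baseline consumption and smoking status at follow-up are already collected, so it needs no new data and no more patients. The cost is the loss of one formal secondary comparison.

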### Data collection

At baseline visit, face to face interview with the sanitary professional will be carried out and the following information will be registered:

– Socio-demographic characteristics: age, gender, civil status, educational level, social class according to the classification of the UK Registrar General's social classification (RGSC).

– E-mail frequently used and data for the telephone tracking.

Characteristics of individual's tobacco consumption: daily consumption in cigarettes/day, years of smoking, age at the start, time before first cigarette of the day, nicotine, dependence measured by the Fagerström test [44], number of previous attempts to quit smoking, maximum time of abstinence, pharmacological treatment used on previous attempts to quit smoking: type, timetable, side effects, family and friends environmental tobacco consumption, partner interaction questionnaire (PIQ Test) to measure of spouse/partner support related to cessation [45].

– Change of stage in the Prochaska and DiClemente's Stages of Change Model.

– Alcohol consumption.

– Morbidity (related or not to tobacco consumption): chronic obstructive pulmonary disease, cerebrovascular event, ischemic cardiopathy, arterial hypertension, hypercholesterolemia, cancer and peripherical arteriopathy, diabetes mellitus, obesity.

– Weight.

– Breath carbon monoxide (CO) in ppm measured by cooximetry which will be carried out by trained health professionals using following a pre-established protocol.

At three months after intervention a second face to face interview will be undertaken with the sanitary professional and the following information will be recorded: time spent in the visit and if the subject currently smokes. If so, daily consumption in cigarettes/day and stage of change according to Prochaska and DiClemente's Stages of Change Model will be recorded. If not, date of smoking cessation, time (in days) of abstinence will be asked, and level of breath CO by cooximetry in standard conditions. Self-reported weight will be documented in both cases. Date of visit and the professional who undertakes it will be additionally recorded.

At six and twelve months after intervention all participants will be asked by phone about some variables related to tobacco consumption and stage of change in the Prochaska and DiClemente's Stages of Change Model (described above) by trained monitors. Moreover, at twelve months after intervention, level of satisfaction, acceptance of intervention, number of E-mail messages written and number of replies and level of social support during the intervention measured by PIQ Test will be recorded.

### Data management and quality assurance

In order to guarantee and to ensure the quality of the study, data to maximize validity and reliability the following measures will be employed:

•Written documentation and electronic data collection: Written copies of protocols and consent forms will be printed and stored in the study web page. All data will be registered in the electronic data collection system developed and maintained specifically for this study by an external company to assure consistency. Regular backups will be performed and transferred to the central database as well as random checks of data entry. If needed, corrections will be made by checking paper records or, in rare cases, by phoning participants for confirmation by independent investigators.

•In order to guarantee the correct registration of data, a training session will be made to all sanitary professionals who participate in the study in the intervention and the use of the electronic data collection system. The contents of the training sessions will be evaluated by completing a standardized evaluation form to ensure the consistency of the program.

•Regular meetings and mailings between members of the study group (the TABATIC team) and all participating centers. Furthermore, a person has been contracted part-time to provide technical and methodological support to all investigators of the study via E-mail or telephone.

•Telephone interviewers will be trained on characteristics and procedures of the study.

### Sample size

Accepting an alpha risk of 0.05 and a beta risk of 0.20 in a bilateral contrast, 1060 individuals are needed; 530 individuals in the IG and 530 in the CG in order to detect a difference of at least a 5% among both groups. A continued abstinence of 5% was assumed for the non intervention group and a dropout rate of 20% is estimated. The sample size calculations were performed with the Granmo program (version 7.1).

### Statistical methods

Data will be analyzed in concordance with the Consort Cluster guide [46], and all analyses will be done on an intention to treat basis. Baseline descriptive statistics among CG and IG in relation to the variables studied will be computed as customary; in contingency tables Pearson’s Chi-square test for independence or homogeneity will be applied to assess the relationship between two categorical variables, T-Student test or ANOVA will be used in the comparison of means if the variables follow a normal distribution and U of Mann Whitney test if they do not. For the other dimensions of the analysis, a covariance analysis (ANCOVA) for repeated measures will be carried out.

A multilevel logistic regression and a Poisson regression will be done to evaluate the association between each of the dependent variables and the independent variables that have resulted statistically significant in the bivariate analysis. All analysis will be adjusted for potential confounding factors and for variables with clinical relevance. The level of statistical significance will be set at 0.05, and all tests will be two-tailed. Statistical analyses will be conducted using SPSS, version 17.0 (SPSS Inc, Chicago, IL).

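### The regression rule picks terms by bivariate significance, does not guarantee that the treatment arm stays in the model, and leaves the adjustment set to the data

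*Protocol article*

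**What the plan says.** Three statements in the protocol article bear on this point.

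- **Statistical methods, term selection.** The regressions relate each dependent variable to "the independent variables that have resulted statistically significant in the bivariate analysis". No separate screening threshold is given. The only level stated is general: "The level of statistical significance will be set at 0.05, and all tests will be two-tailed".
- **Statistical methods, next sentence.** "All analysis will be adjusted for potential confounding factors and for variables with clinical relevance". No variable is named, and no rule for choosing variables is given.
- **Outcome measures, under Independents.** There is one entry: "Type of intervention: Intensive counseling by E-mail vs brief advice".

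No sentence says that the arm enters every model whatever its p-value. Nor does the text say how the two adjustment sentences relate to each other.

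**The concern.** This is a stated rule, not detail left to a fuller document. It has two weaknesses.

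First, the wording does not protect the treatment term. If the independent variables are those that the article itself labels as such, the arm is subject to the screen. A treatment effect that is modelled and reported only after passing a significance test on the same data is, on average, too large.

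Second, even with the arm kept, the covariates are chosen by p-values from the trial's own data, separately for each dependent variable. The main outcome at 6 months and at 12 months could then be adjusted for different variables. Odds ratios conditional on different covariate sets do not estimate quite the same quantity. A genuine predictor can also be left out because it narrowly misses 0.05. The clinical-relevance sentence might bring it back, but that is a judgement which nothing obliges the team to make before seeing outcomes.

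**Working it through.** **1. The plan's own figure.** Inputs from Sample size: "Accepting an alpha risk of 0.05 and a beta risk of 0.20 in a bilateral contrast, 1060 individuals are needed", "in order to detect a difference of at least a 5% among both groups" and "A continued abstinence of 5% was assumed for the non intervention group and a dropout rate of 20% is estimated". So the rates are 5% and 10%, two-sided alpha is 0.05 and power is 0.80.

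Arcsine formula: n = 2(z₀.₉₇₅ + z₀.₈₀)² / h², with h = 2·asin√0.10 − 2·asin√0.05 = 0.1925.
n = 2 × 7.849 / 0.03705 = 423.7, so 424 per arm. Allowing for dropout, 424 / 0.80 = 530 per arm, 1060 in total. The stated figure is reproduced exactly.

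**2. If the arm is screened and reported only when it passes.** 400,000 simulated trials per setting, control rate 5%, pooled two-sided z-test at 0.05, no clustering. The odds ratio (OR) is a geometric mean over the trials that pass. The true intervention rates below 10% are assumptions.

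| True rate, intervention | True OR | 530/arm: arm passes | Mean difference if it passes | OR if it passes | 424/arm: OR if it passes |
|---|---|---|---|---|---|
| 10% | 2.111 | 88% | 5.4 points (true 5.0) | 2.230 | 2.319 |
| 8% | 1.652 | 51% | 4.2 points (true 3.0) | 2.016 | 2.145 |
| 7% | 1.430 | 28% | 3.8 points (true 2.0) | 1.964 | 2.101 |
| 6% | 1.213 | 11% | 3.2 points (true 1.0) | 1.866 | 1.965 |

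The 530 column treats all randomised patients as analysed, in line with the stated intention-to-treat basis. The 424 column is the completer case. With no true effect, positive and negative passes cancel and the average signed difference is about zero.

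**3. If the arm is always kept and only covariates are screened.** 2,000 simulated trials per setting, 530 per arm. Assumed: eight independent standard-normal covariates with log-odds slopes 0.5, 0.3, 0.2 and five zeros, screened against the outcome at 0.05.

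| True log-OR | Mean, screened covariates | Mean, all eight prespecified | Rejection, screened | Rejection, prespecified |
|---|---|---|---|---|
| 0 | −0.009 | −0.009 | 0.050 | 0.048 |
| 0.40 | 0.411 | 0.415 | 0.338 | 0.339 |
| 0.75 | 0.756 | 0.763 | 0.852 | 0.860 |

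The Monte Carlo standard error of the type I error is √(0.05 × 0.95 / 2000) = 0.005. Bias is immaterial, type I error is about 5%, and the power lost to screening is under one percentage point.

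**4. How often a true predictor is discarded.** At 5% versus 10% with 530 per arm, about 26.5 + 53 = 79.5 abstainers are expected. The standard error of a log-OR per standard deviation is about 1/√(530×0.05×0.95 + 530×0.10×0.90) = 1/√72.9 = 0.117.

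- Assumed OR 1.3 per SD: z = 0.262/0.117 = 2.24. The chance of missing 0.05 is Φ(1.96 − 2.24) = about 39%.
- Assumed OR 1.2 per SD: z = 0.182/0.117 = 1.56. The chance is Φ(1.96 − 1.56) = about 66%.

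So whether a moderate predictor enters the model is largely a matter of chance, and it can easily enter at one time point and not at the other.

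**The case against.** The literal reading can fairly be called strained. Statistical methods speaks of independent variables in the plural, whereas Outcome measures lists only one, so the two lists cannot be the same. Study design gives the comparison of the arms as the purpose of the trial, and a model without the arm could not serve it. The clinical-relevance sentence also means that significance is not the only way into the model; stage of change or nicotine dependence could enter by that route. All of this stands. It shows that dropping the arm is probably not intended, but the text still does not rule it out.

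A reader might infer that the adjusted treatment effect will be biased away from no effect. The documents do not support that as a general statement. It needs both that the arm is screened and that its effect is reported only when it passes. With the arm kept, step 3 shows no such bias. The exaggeration in step 2 is what any trial shows when its estimate is taken conditional on significance, and the proportions passing are simply power.

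A reader might also infer that covariates are picked by testing baseline variables between arms, with many chance hits. The baseline sentence, "Baseline descriptive statistics among CG and IG in relation to the variables studied will be computed as customary", describes a descriptive comparison, and the regression sentence concerns association with the outcomes. The text does not specify selection against arm.

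Finally, an article may leave its exact covariate list to a fuller document. That is fair, but the objection here is to the selection rule which the article does state.

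**Conclusion.** The point holds in a limited form. The term-selection rule is poor, sits unreconciled beside a second adjustment rule, and does not secure the treatment term. Under the literal reading, with reporting only on passing, the exaggeration at 530 per arm is modest at the design effect (OR 2.23 against 2.11) and larger for smaller true effects (2.02 against 1.65 at 5% versus 8%). Under the ordinary reading, with the arm kept, the treatment estimate and the type I error are essentially unharmed. What remains is an adjustment set that is chosen from the data, may differ between 6 and 12 months, and may omit true predictors.

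These sizes rest on the planned 5% control rate, on assumed intervention rates and covariate strengths, and on ignoring clustering by professional. This is an improvement available at no cost, not a fault that invalidates the planned analysis.

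**What to change.** In Statistical methods:

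- Delete the bivariate-significance rule.
- State that the arm is in every model whatever its p-value.
- Fix one primary multilevel model for continuous abstinence with a short list of baseline prognostic covariates, for example stage of change, Fagerström score and cigarettes per day. Name them before any outcome is seen and use the same list at 6 and 12 months.
- Let that list replace the open-ended sentence on confounders and clinical relevance.
- Report the unadjusted result alongside.

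The cost is a few lines of text. Data collection already records all three covariates at baseline, and the sample size and visits do not change.
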